### Patients

#### Study population and sample size

This study focuses on women experiencing perimenopausal syndrome. According to the previous study by Guang’anmen Hospital, China Academy of Chinese Medical Sciences (results still unpublished), the improvement of Menopause Rating Scale (MRS) scores of the electro-acupuncture group and the sham acupuncture group were 6.5 and 2, respectively. The difference in scores between the two groups was 4.5, and electro-acupuncture was not superior to sham acupuncture. Accordingly, we assume that a difference within 4.5 indicates acupuncture is not inferior to Climen® treatment. Using a non-inferiority design, and assuming a power of 90%, an alpha value of 5%, and a population standard deviation of 10, a total of 206 patients will be needed in this study. Each group needs 103 patients (assuming a 20% dropout rate).

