### Statistical analysis

All data from this study will be analyzed by special analysts with SPSS 20.0 (IBM Corp., Armonk, NY, USA).

The tests of outcomes are based on the intention-to-treat population. Sensitivity analyses are performed for the primary outcomes (MRS measured 16 weeks after randomization) by replacing missing data with multiple imputations and lost observations carried forward using SPSS 20.0. Multiple imputations are calculated using the propensity score method. The MRS is used as a dependent variable in an analysis of covariance, with the groups as random factors, and with baseline MRS and age as covariates, to account for potential baseline differences. Adjusted mean treatment effects are given alongside corresponding 95% confidence intervals and *P* values. The same analysis method will be performed for all secondary outcomes.

In addition to the above analysis, we will perform an exploratory analysis to describe group means over time. We will calculate summary statistics to reveal whether the two groups are changing in a similar or different fashion. A two-sided test is applied for available data, and *P* < 0.05 is considered statistically significant.

There is one acupuncturist in each center to do all treatment, which probably introduces a clustering effect in this trial. We therefore calculated the intracluster correlation coefficient from the result of this trial and report the coefficient [28].

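### The plan expects clustering by the single acupuncturist in each centre, but its 90% power and its ANCOVA treat patients as independent, and an ICC from three clusters cannot show whether that mattered

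*Protocol article*

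**What the plan says.** The section on study population and sample size sets a non-inferiority comparison of AA with Climen®, in which "we assume that a difference within 4.5 indicates acupuncture is not inferior to Climen® treatment". Its remaining inputs are given as "assuming a power of 90%, an alpha value of 5%, and a population standard deviation of 10", plus 20% dropout. The result is 103 per arm, 206 in total, recruited at three hospitals. No ICC, cluster size or design effect is among the inputs.

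The Statistical analysis section specifies an ANCOVA of the MRS on group, with baseline MRS and age as covariates. It then acknowledges a further source of variation: "There is one acupuncturist in each center to do all treatment, which probably introduces a clustering effect in this trial". The response is one sentence: "We therefore calculated the intracluster correlation coefficient from the result of this trial and report the coefficient". No centre or acupuncturist term enters the model.

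**The concern.** The plan names a departure from independence as probable and then sizes and analyses the trial as if it were absent. If women treated by the same acupuncturist have correlated outcomes, the AA mean is less precise than the formula assumes. There are two possible consequences, depending on the analysis.

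- If the analysis ignores the correlation, its standard error is too small. Non-inferiority is then claimed too often when AA is in truth worse by the full margin. Power also falls somewhat.
- If the analysis allows for the correlation, the error rate is protected but power falls well below 90%.

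Reporting an ICC afterwards repairs neither. An estimate from three clusters is very imprecise. Because each acupuncturist works in only one hospital, an ICC taken over all patients also cannot tell acupuncturist from hospital.

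**Working it through.** **Inputs from the protocol article.** Margin 4.5, SD 10, power 90%, alpha 5%, dropout 20%, 103 per arm, three hospitals, one acupuncturist in each.

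**Assumptions.** True difference 0 for power; one-sided 5% (the sample-size section gives no sidedness); equal recruitment across centres; acupuncturists as a random sample; clustering in the AA arm only, since a hospital effect common to both arms largely cancels under 1:1 randomisation; no precision gain from baseline adjustment; ICC 0.01 to 0.10.

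**Step 1: the plan's figure.** n per arm = 2 × 10² × (1.645 + 1.282)² / 4.5² = 84.6, so 85, or 86 with the t distribution. Multiplying by 1.2 for dropout gives 102 or 103.2, which matches 103. At one-sided 2.5% the formula gives 104 before dropout, close to 103 but with nothing left for dropout. Neither route contains a design effect. The first is used below, with 86 evaluable per arm.

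**Step 2: true and assumed standard errors.**

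- Cluster size m = 86/3 = 28.7; design effect DE = 1 + (m − 1) × ICC.
- SE if independent: SE₀ = 10 × √(2/86) = 1.525.
- SE with AA-arm clustering: SE₁ = 10 × √((1 + DE)/86).

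**Step 3: operating characteristics (normal approximation).**

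- Analysis ignoring clustering: power = Φ((4.5 − 1.645 × SE₀)/SE₁); false non-inferiority rate at the margin = 1 − Φ(1.645 × SE₀/SE₁).
- Analysis allowing for clustering: power = Φ(4.5/SE₁ − 1.645).

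| ICC | DE | Effective AA n (86/DE) | SE₁ | Power, ignoring | False non-inferiority, ignoring | Power, allowing |
|---|---|---|---|---|---|---|
| 0 | 1.00 | 86 | 1.525 | 90.4% | 5.0% | 90.4% |
| 0.01 | 1.28 | 67 | 1.627 | 89% | 6% | 87% |
| 0.02 | 1.55 | 55 | 1.723 | 88% | 7% | 83% |
| 0.05 | 2.38 | 36 | 1.983 | 84% | 10% | 73% |
| 0.10 | 3.77 | 23 | 2.354 | 80% | 14% | 61% |

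Example at ICC 0.05: (4.5 − 1.645 × 1.525)/1.983 = 1.00, power 84%; 1.645 × 1.525/1.983 = 1.265, error 10.3%; 4.5/1.983 − 1.645 = 0.62, power 73%.

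The last column is optimistic. A t reference with the roughly 3 to 6 degrees of freedom that three acupuncturists allow lowers it to about 79, 73, 59 and 45%.

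**Step 4: what the reported ICC can show.** Take three clusters of 29 (2 and 84 degrees of freedom). An observed ICC of 0.05 corresponds to F = (1 + 28 × 0.05)/(1 − 0.05) = 2.53. Dividing by 3.86 and multiplying by 39.5 (the 97.5% F points) and converting back by (F − 1)/(F + 28) gives a 95% interval of about −0.01 to 0.77. If the true ICC is 0.05, the estimate is zero or negative in about 33% of trials; if 0.02, in about 46%.

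**The case against.** **Which analysis loses the power.** A reader might infer that the planned analysis has only 73% power at ICC 0.05. The documents do not support that. The ANCOVA has no cluster term, so its own figure is about 84%. The 73% belongs to a cluster-allowing test that the article does not specify. What stands for the analysis as written is a smaller loss of power together with an inflated error rate.

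**Baseline adjustment.** SD 10 may be unadjusted, and the ANCOVA adjusts for baseline MRS. Suppose a baseline correlation of 0.5 (not in the documents) that reduces patient-level variance only: SE² = 75 × (2 − ICC)/86 + 100 × ICC/3. Power allowing for clustering is then 93, 90 and 79% at ICC 0.01, 0.02 and 0.05. At correlation 0.3 it is 89, 86 and 75%. So a shortfall at small ICCs is not certain. The adjustment does not cure the error rate, however. At correlation 0.5 and ICC 0.05 the model's SE is 10 × √(0.75 × 2/86) = 1.32 against a true 1.84, and the error is about 12%.

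**Fixed acupuncturists.** If inference is confined to these three people, the loss does not arise. This is a sound position, but the article does not take it, and its Discussions section places the trial in a programme meant to inform practice guidance. A standardised point protocol, training with an examination and monthly monitoring may keep the ICC small; no value is given.

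**Evaluable number.** Losing 20% of 103 leaves 82.4, not 86. Power before clustering is then 89.3%, so the choice of 86 does not exaggerate the problem.

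**Purpose of the ICC.** A reader might infer that the ICC was meant to supply the missing power allowance. The article says only that it will be calculated and reported. The criticism is that, so reported, it tells almost nothing.

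**Conclusion.** The point holds. The 90% power assumes independent patients, while the same article calls clustering by acupuncturist probable, and the planned analysis makes no provision for it. On the stated assumptions, across ICC 0.01 to 0.10 the analysis as written drops to about 89 to 80% power, and its false non-inferiority rate rises from 5% to about 6 to 14%. An analysis that allows for clustering would have about 87 to 61% power. The direction follows from any positive ICC if the acupuncturists are regarded as a sample; the size depends on an ICC the documents do not give.

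A reader might also conclude that the sample size was miscalculated or must be raised. That goes too far. The arithmetic reproduces for independent patients, and with only three acupuncturists more patients would help little: at ICC 0.10 the term 100 × 0.10/3 = 3.33 alone exceeds the variance that 90% power permits, (4.5/2.927)² = 2.36. What needs correcting is the statement of power, the scope of the conclusion and the analysis.

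**What to change.** No change in patient numbers is needed.

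1. **Sample size section.** State that the 90% assumes no acupuncturist clustering, or applies only to these three acupuncturists. Give power for ICC 0.01 to 0.05 for the analysis actually used, and state the sidedness of alpha.
2. **Statistical analysis section.** Choose one of two routes. Either limit the conclusion to these three acupuncturists as fixed and put centre in the ANCOVA, or add a sensitivity analysis whose standard error allows for clustering in the AA arm, with a reference distribution suited to three clusters.
3. **Reporting.** Give the AA-minus-Climen® MRS difference in each centre with its 95% interval, and repeat the primary estimate leaving out one centre at a time, both as description. Compute any ICC in the AA arm and show its interval.

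Item 3 has limits. Within-centre differences remove hospital effects shared by both arms, but do not separate the acupuncturist from other differences in treatment effect between centres. With about 29 women per arm per centre the half-width is 1.96 × 10 × √(2/29) = 5.1 points, wider than the 4.5 margin, so these intervals cannot prove or exclude dependence on one practitioner.

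The cost is wording and a few extra models. The stated power becomes less favourable, and the sensitivity analysis will be imprecise.

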## Discussions

This trial is sponsored and financially supported by the National Key Technology R&D Program during the Twelfth Five-year Plan Period of China. The study reported in this article is only one part of this program, which is an international multicenter systematic evaluation of clinical effectiveness of acupuncture. The purposes of this international collaborative program are to prove the therapeutic effects and safety of acupuncture and to establish guidelines for clinical practice. The result of this trial is expected to provide convincing evidence that acupuncture is effective for patients with perimenopausal syndrome.

Previous RCTs show acupuncture in the treatment of symptoms of both perimenopausal and postmenopausal females has no advantage, compared with placebo needles [16-19]. Compared with no medical treatment (for example, self-caring, waiting), however, acupuncture is able to relieve symptoms quite well [16,17,29]. In view of controversial results, some researchers asserted that the placebo needles might have similar effects to verum acupuncture [30], and this view may underestimate the total effectiveness of verum acupuncture. We are therefore conducting a pragmatic trial that requires a positive drug as the control group to clarify an acupuncture therapeutic effect rather than a placebo needle. Moreover, we use a non-inferiority method to estimate the sample size, and only include perimenopausal patients. What we expect is to prove the therapeutic effects of acupuncture on perimenopausal syndrome, and provide another alternative treatment for perimenopausal women.

HRT has been in use for more than half a century and is regarded as a gold standard treatment for vasomotor, urogenital symptoms and their potential consequences such as sleep problems, and mood disorders [31-33]. HRT can improve the health-related quality of life through the alleviation of these symptoms. Meanwhile, HRT is beneficial to prevent aging women from osteoporosis, metabolic syndrome, and cardiovascular problems [4]. HRT is thus an ideal treatment for females with perimenopausal syndrome. Given all patients in this trial have an intact uterus, we choose estrogen plus progestin therapy to negate the risk of endometrial cancer rather than using estrogen alone, and 12-week treatment for women aged 40 to 55 should be safe according to the statement of the North American Menopause Society [4]. Furthermore, studies have shown that sequential estradiol valerate and cyroterone acetate combinations: relieve climacteric complaints via increasing serum estrogen, and provide a good menstrual cycle inducing a physiological secretory transformation of the endometrium without side effects [34]; exert a positive effect on body fat mass and distribution [35]; and may have protective effects for postmenopausal bone loss [36]. We therefore chose Climen® as a positive drug control.

We chose the MRS as the primary outcome, which was initially developed to measure the severity of aging symptoms and their impact on health-related quality of life in the 1990s [37]. Three different dimensions of symptoms (psychological, somato-vegetative, and urogenital symptoms) are measured by 11 items, which can be easily completed by women themselves rather than physicians [37,38]. The total scores of MRS vary between 0 (no symptom) and 44 (highest degree of symptoms) based on the severity of symptoms; the higher scores patients obtain, the more serious symptoms they have. Since 1992 the MRS has been developed and proven to be reliable and valid for decades [39,40]. This self-assessment scale has the following objectives: to enable comparisons of the symptoms of aging between groups of women under different conditions; to compare severity of symptoms over time; and to measure changes before and after treatment [36-38]. Since the English version was published [41], 24 different languages versions are now available on the website [42]. Due to its reliability and validity, we chose the MRS as the primary outcome of this trial to assess perimenopausal syndrome. We chose Menopause-Specific Quality of Life as one of the secondary outcomes to assess the severity of these symptoms affecting patients’ life quality. To measure the severity and frequency of hot flashes and sweats, participates will be required to fill hot-flash dairies for 1 week before each measurement point. The average hot-flash score during 24 hours is the 7-day total score of severity (0, none; 1, mild; 2, moderate; 3, severe)/7.

One recent RCT found that traditional acupuncture continued relieving the vasomotor symptoms throughout the 3-month treatment period, while the sham acupuncture was tending towards stability after the first month [17]. A longer duration of treatment was hypothesized to be a superior effect between traditional and sham acupuncture. Accordingly, in order to observe a significant effectiveness of acupuncture, participants in our study will receive 3 months of treatment. Another study indicated that the effectiveness of acupuncture on perimenopausal syndrome was superior to HRT during the 6-month follow-up period [43]. Therefore, it is necessary to conduct a longer period of follow-up to obverse the continuous effects of acupuncture compared with positive drug, and also to assess the safety after treatment. Before this trial we conducted a questionnaire survey of 156 women with perimenopausal syndrome in the First Affiliated Hospital of Chengdu University of TCM to obtain the public’s acceptance and understanding of acupuncture treatment for perimenopausal problems (the detail of this survey will be available soon). According to the results of the survey, previous RCTs and the opinions of experts, we designed this protocol for better treatment and follow-up arrangements.

Our study still has limitations. Firstly, the whole research period of this study is 37 weeks (1 week baseline, 12 weeks of treatment and 24 weeks of follow-up) and may increase the rate of patient drop-out. We therefore reduce the treatment demand after the first month of treatment and keep close contact with our patients via telephone calls, short messages, emails, and so forth, during the follow-up period, to decrease the drop-out rate. Secondly, the three centers of this study are in Chengdu, which is a capital city located in the southwest of China, and the patients we will include in this trial are mostly local residents. The population may therefore not represent the advantages of a multicenter study. Thirdly, participants assigned to the acupuncture group may have more opportunities for contact with their acupuncturists and build a good doctor–patient relationship rather than those of the control group, which may improve the therapeutic effect [44]. We will therefore keep close contact with patients in the control group by telephone, Internet, and so on, to decrease this potential bias. Meanwhile, it is difficult to blind patients after randomization due to the specificity of acupuncture. We therefore strictly conduct central randomization and appoint different people to perform therapy, measurement and statistical analysis.

Owing to a lack of solid evidence for effectiveness of acupuncture treatment on perimenopausal syndrome, this trial aims to clarify this issue by means of a multicenter randomized controlled large-scale trial.

In conclusion, the results of this trial are expected to confirm whether acupuncture is effective in relieving perimenopausal syndrome.

## Trial status

This trial is currently in the recruitment phase.

## Abbreviations

HRT: hormone replacement therapy; MRS: Menopause Rating Scale; RCT: randomized controlled trial; TCM: traditional Chinese medicine.
